### **7.5 Withdrawal Visit**

No early termination or withdrawal visits are anticipated, but in the event that this occurs, such a visit would follow the same guidelines established for a final study visit as long as the parent/caregiver is willing.

### **7.6 Unscheduled Visit**

No unscheduled visits are anticipated. All adverse events will be reported as outlined in Section 9.

---

## **8 STUDY PROCEDURES / EVALUATIONS**

### **8.1 Study Procedures/Evaluations**

The clinical procedures and evaluations for this study will consist of the following: Child's medical history will be evaluated via a standardized questionnaire administered to the parent/caregiver at the dental screening visit. A dental provider will perform a dental screening examination and will obtain a plaque score on the buccal surfaces of anterior teeth after application of disclosing solution, following the Debris Index of the Oral Hygiene Index (Greene and Vermillion). Photographs of anterior teeth will be taken with the study camera to record plaque levels. After study staff demonstrate and observe parent/caregiver performance of study procedures, the dental provider will apply fluoride varnish.

### **8.2 Questionnaires**

Research staff will administer CAPI Questionnaires to parents/caregivers during the study visits at baseline and 2-month follow-up, with data entered directly into Qualtrics; questionnaire data will be analyzed for changes in self-reported behaviors and perceptions, including relevant common data elements (CDEs) identified by NIDCR OHDC Collaborative Working Groups. Questionnaire items include demographics, current brushing behaviors, dental visit attendance drawn from BRFQ (Albino et al., in submission), economic module, and POQL (Huntington et al. 2011). Follow-up questionnaires will assess satisfaction/acceptance of the incentives and study procedures, as well as compliance with study procedures, such as whether others in the household used the child's powered toothbrush or toothpaste pump.

### **8.3 Anticipatory Guidance**

A short health education video in English or Spanish will provide parents/caregivers with key preventive oral health messages appropriate for the child's age, such as the importance of fluoride supplements, healthy snacking and how to prevent the spread of bacteria that causes caries.

### **8.4 Toothbrushing Performance and Frequency**

#### **8.4.1 *Toothbrushing Diaries***

Parents/caregivers will be given calendar diaries to track toothbrushing events that can be compared to the smart powered TB's data. The calendar will be explained at baseline by research staff and collected at follow-up.

#### **8.4.2 *Smart Toothbrushes***

During the baseline visit, all participants will receive a "smart" powered TB (e.g. Philips Oral Healthcare). The TB uses Bluetooth technology to transmit data on brushing timing,

frequency, and duration from the TB to an app installed on the participant's smartphone. Every week, the vendor (e.g. Philips Oral Healthcare) will transmit or provide a secure login to access an encrypted, de-identified file containing participants' brushing data to study investigators.

## **8.5 Dental Visit Attendance**

Preventive dental visit attendance of participating children will be ascertained through dental exam data from Head Start's ChildPlus Management Software health module. In the subset of children at baseline without any dental visit in the Early Head Start ChildPlus health module, whether or not the child has a ChildPlus documented dental visit at the two-month follow-up will be assessed.

## **8.6 Study Products**

The Program Manager will maintain a log of disclosing solution and TP shipments, including batch numbers and expiration dates. The study products will be stored in the Program Manager's office at UCLA.

### **8.6.1 *Plaque Disclosing Solution***

At each in-person visit, the dental provider will apply GUM Red-Cote Liquid plaque disclosing agent to the child's teeth for plaque assessment.

### **8.6.2 *Fluoride Varnish***

Vanish Fluoride Varnish (3M) is a varnish that is applied to the teeth and enhances enamel acid and boosts salivary fluoride levels. The product contains fluoride, calcium and phosphate, which helps the product remain on the teeth longer and provides extra protection. Vanish can be applied quickly without color change to the teeth. A dental clinician will apply the disclosing solution with a brush.

### **8.6.3 *Fluoride Toothpaste Pump***

Study participants will be instructed to use fluoridated TP based on the recent ADA consensus guideline (2014) that recommends all children use fluoride TP to help prevent dental disease. The study will use Colgate Maximum Cavity Protection Pump Fluoride Toothpaste (Colgate-Palmolive Company) (mild bubble fruit flavored).

The parents/caregivers will be instructed on how to dispense a smear or pea-sized amount (depending on child's age) of fluoride TP onto the TB for the child, as per study guidelines.

If a child experiences an adverse reaction to the fluoride TP, he/she will be provided clinical guidance (e.g., discontinue use of the product); based on clinical judgment and appropriate input from oversight groups, use may be re-started. However, no modification of study product dosage will be made.

## 9 ASSESSMENT OF SAFETY

### 9.1 Specification of Safety Parameters

The principal investigator (PI) will report safety events for the study (unanticipated problems [UPs], adverse events [AEs], serious adverse events [SAEs]) to the Institutional Review Board (IRB) in accordance with the IRB's requirements.

The PI will also report UPs involving risks to subjects to NIDCR. This will include UPs that meet the definition of a SAE. AEs that are temporally associated with the administration by study personnel of fluoride varnish will be recorded in an adverse event log, and this log will be monitored to identify events that meet the definition of a UP. If a UP is identified, it must be reported.

#### 9.1.1 *Unanticipated Problems (UPs)*

The Office for Human Research Protections (OHRP) considers unanticipated problems (UPs) involving risks to subjects or others to include, in general, any incident, experience, or outcome that meets **all** of the following criteria:

- Unexpected in terms of nature, severity, or frequency given (a) the research procedures that are described in the protocol-related documents, such as the IRB-approved research protocol and informed consent document; and (b) the characteristics of the subject population being studied;
- Related or possibly related to participation in the research ("possibly related" means there is a reasonable possibility that the incident, experience, or outcome may have been caused by the procedures involved in the research); and
- Suggests that the research places subjects or others at a greater risk of harm (including physical, psychological, economic, or social harm) than was previously known or recognized.

#### 9.1.2 *Adverse Events*

OHRP defines an adverse event as any untoward or unfavorable medical occurrence in a human subject, including any abnormal sign (for example, abnormal physical exam or laboratory finding), symptom, or disease, temporally associated with the subject's participation in the research, whether or not considered related to the subject's participation in the research (modified from the definition of adverse events in the 1996 International Conference on Harmonization E-6 Guidelines for Good Clinical Practice).

In this study, due to the anticipated low risk of products being used, AEs that are not acute with onset within three days of product administration or were not medically attended events, serious AEs (SAEs) or unanticipated problems related to the intervention (UPs) will not be collected.

SAEs and UPs will be captured throughout the study period.

All reportable AEs will be graded for severity and relationship to the study product (see Section 9.3.3).

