## 9.2 **Time Period and Frequency for Event Assessment and Follow-Up**

AEs, UPs and SAEs will be recorded in the data collection system throughout the study. Events will be followed for outcome information until resolution or stabilization.

The Study PI will record all reportable events with start dates occurring any time after informed consent is obtained until seven (for non-serious AEs) or 30 days (for SAEs) after the last day of study participation. Parents/caregivers will be instructed to report any doctor office or emergency room visits in the three days after the fluoride varnish application. At the 2-month follow-up (final) study visit, the investigator will inquire about the occurrence of AE/SAEs including FV-related AE/SAEs since the last visit. Events will be followed for outcome information until resolution or stabilization.

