### 9.3.3 ***Severity of Event***

Severity of Event: All reportable AEs will be assessed by a clinician study PI or co-investigator using the following guidelines to quantify intensity:

- 1) Mild: events require minimal or no treatment and do not interfere with the participant's daily activities.
- 2) Moderate: events result in a low level of inconvenience or concern with the therapeutic measures. Moderate events may cause some interference with functioning.
- 3) Severe: events interrupt a participant's usual daily activity and may require systemic drug therapy or other treatment. Severe events are usually incapacitating

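### As worded, the adverse-event rule in Protocol 9.1.2 drops acute varnish reactions that were not medically attended, which Protocol 9.1 requires to be logged

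*Protocol*

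**What the plan says.** Three parts of Protocol Section 9 govern which adverse events are recorded.

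- **9.1 (Specification of Safety Parameters):** "AEs that are temporally associated with the administration by study personnel of fluoride varnish will be recorded in an adverse event log". The sentence sets no condition of medical attention and no day limit. It gives the log a purpose: "this log will be monitored to identify events that meet the definition of a UP".
- **9.1.2 (Adverse Events):** citing the low risk of the products, it removes from collection "AEs that are not acute with onset within three days of product administration or were not medically attended events". The second exclusion also names SAEs and intervention-related UPs next to attended events. A separate sentence then adds: "SAEs and UPs will be captured throughout the study period".
- **9.2 (Time Period and Frequency):** "AEs, UPs and SAEs will be recorded in the data collection system throughout the study". Reportable events count if they start "any time after informed consent is obtained until seven (for non-serious AEs) or 30 days (for SAEs) after the last day of study participation". The investigator asks about adverse events at the 2-month visit, including those related to varnish. The same section instructs parents to report doctor or emergency visits in the three days after varnish.

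Section 2.3.1 tells parents to contact the Program Director if they suspect an allergic reaction to a study product. It refers the reporting of adverse reactions to Section 9.

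**The concern.** The exclusion in 9.1.2 is written as two negatives joined by 'or'. Read as it stands, an event is discarded when it fails either test, so an ordinary event must pass both to be kept. Section 9.1 applies no such double test to varnish reactions.

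This matters because the log described in 9.1 is screened to identify UPs. A reaction that is never entered cannot be recognised through that log. The sentence in 9.1.2 that keeps UPs therefore protects only partly against the filter: the UP must first be recognised by some other route. Staff at up to three sites could also apply Section 9 differently, because it supports two incompatible rules.

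**Working it through.** No sample size or power figure is involved. The check is a truth table plus a side-by-side reading.

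**Definitions.** A = acute with onset within three days of product administration. M = medically attended. S = SAE or UP.

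**Three readings.**

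1. Literal 9.1.2: exclude if (not A) or not (M or S). Collect only if A and (M or S).
2. Literal 9.1.2 plus its next sentence: collect if [A and (M or S)] or S.
3. Conditions as alternatives: exclude only if (not A) and not (M or S). Collect if A or M or S.

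| A | M | S | Reading 1 | Reading 2 | Reading 3 |
|---|---|---|---|---|---|
| yes | yes | yes | collected | collected | collected |
| yes | yes | no | collected | collected | collected |
| yes | no | yes | collected | collected | collected |
| yes | no | no | dropped | dropped | collected |
| no | yes | yes | dropped | collected | collected |
| no | yes | no | dropped | dropped | collected |
| no | no | yes | dropped | collected | collected |
| no | no | no | dropped | dropped | dropped |

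The readings collect 3, 5 and 7 of the 8 classes. Among the four non-serious, non-UP classes (S = no), reading 2 collects one and reading 3 collects three. These are counts of logical classes, not of events.

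**Class by class against the other sections.**

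- *Acute, unattended, non-serious, non-UP* (for example, hives the day after varnish that settle at home). Section 9.1 requires logging if the event is temporally associated with varnish. Readings 1 and 2 of 9.1.2 drop it. This is a direct conflict.
- *Attended, but not acute within three days, non-serious, non-UP.* Readings 1 and 2 drop it. Section 9.1 does not clearly require it, because it does not define temporal association. The tension here is with 9.2, which records adverse events across the study and keeps the non-serious window open until seven days after participation ends. Varnish is applied only at baseline (7.2 and Appendix A). If the three-day clock runs from varnish, the literal rule leaves little of a non-serious kind for the 2-month inquiry to collect.
- *SAEs and UPs.* Reading 1 would drop those outside the three-day window; the next sentence of 9.1.2 restores them.

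**The window.** 9.1.2 says only product administration. Section 8.6 lists disclosing solution, varnish and fluoride toothpaste as study products, and toothpaste is meant for twice-daily use. If each brushing counts as an administration, the window hardly closes and a later attended event could still fall inside it. If only clinic-applied products count, it closes three days after the visit.

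**The case against.** The strongest reply is that nobody would apply the sentence literally. Taken alone it would drop a late SAE, and the next sentence shows that this is not meant. That supports a drafting slip, but it does not say what happens to non-serious events, which the next sentence does not mention.

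A second reply points to other safeguards: the call to the Program Director, the open question at 2 months, the principal investigators' regular safety review, and capture of SAEs and UPs throughout. These mean that a home-managed reaction may well reach staff, and that the log is not the only route to a UP. They do not settle whether the reaction is recorded, because recording still follows Section 9.

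Several stronger inferences are tempting and are not supported:

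- A reader might conclude that the authors plainly meant the conditions as alternatives. The parent instruction in 9.2, limited to doctor or emergency visits within three days, fits the both-required reading, so intent is open.
- A reader might conclude that losing attended events after day three also contradicts 9.1. That is not shown: temporal association is undefined there, and the product that starts the window is not named.
- A reader might think that the mild grade in 9.3.3 becomes unusable. Its definition ("events require minimal or no treatment" and no interference with daily activities) does not turn on attendance. An office visit ending in reassurance can be mild.
- A reader might treat the class counts as a share of events lost, or predict near-zero reported reactions carried into the later trial. The protocol gives no event rates, and reaction incidence is not among the outcome measures in 3.2.

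**Conclusion.** The point holds in a limited form. As written, 9.1.2 collects a non-serious, non-UP adverse event only when it is both acute within three days and medically attended. For acute, unattended varnish reactions this directly contradicts the logging requirement in 9.1. It also fits poorly with 9.2, which combines study-long recording and an open inquiry at 2 months with a narrow instruction to parents.

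The firm part assumes only that an acute reaction within three days of varnish is temporally associated with it. Loss of later attended events is conditional on the window running from varnish or another clinic-applied product. The number of affected events cannot be estimated from the protocol. This is an inconsistency in a safety-collection rule that should be corrected; it does not affect the outcome comparisons.

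**What to change.** Reconcile 9.1, 9.1.2 and 9.2 into one rule stated positively, that is, by listing what is collected. It should:

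1. say whether acute onset within three days and medical attention are alternatives or are both required for non-serious, non-UP events;
2. name the product administration that starts the three-day window;
3. keep the logging of varnish-associated adverse events promised in 9.1, with an explicit exception if both conditions are otherwise required;
4. keep capture of SAEs and UPs throughout.

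Then align the parent instruction in 9.2 and the eCRF entry check with that rule. If the conditions are meant as alternatives, the smallest edit to 9.1.2 is to replace 'or were not' with 'and were not'. Which rule applies is for the investigators to decide.

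The cost is a short text amendment, one eCRF check, and a few more non-serious events logged among 36 children.

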### 9.1.3 ***Serious Adverse Events (SAEs)***

A serious adverse event (SAE) is one that meets one or more of the following criteria:

- Results in death.
- Is life-threatening (places the subject at immediate risk of death from the event as it occurred).
- Results in inpatient hospitalization or prolongation of existing hospitalization.
- Results in a persistent or significant disability or incapacity.
- Results in a congenital anomaly or birth defect.
- An important medical event that may not result in death, be life threatening, or require hospitalization may be considered an SAE when, based upon appropriate medical judgment, the event may jeopardize the subject and may require medical or surgical intervention to prevent one of the outcomes listed in this definition.

## 9.2 **Time Period and Frequency for Event Assessment and Follow-Up**

AEs, UPs and SAEs will be recorded in the data collection system throughout the study. Events will be followed for outcome information until resolution or stabilization.

The Study PI will record all reportable events with start dates occurring any time after informed consent is obtained until seven (for non-serious AEs) or 30 days (for SAEs) after the last day of study participation. Parents/caregivers will be instructed to report any doctor office or emergency room visits in the three days after the fluoride varnish application. At the 2-month follow-up (final) study visit, the investigator will inquire about the occurrence of AE/SAEs including FV-related AE/SAEs since the last visit. Events will be followed for outcome information until resolution or stabilization.

## 9.3 **Characteristics of an Adverse Event**

### 9.3.1 ***Relationship to Study Intervention***

To assess relationship of an event to study intervention, the following guidelines are used:

1. Related (Possible, Probable, Definite)
  - a. The event is known to occur with the study intervention.

- b. There is a temporal relationship between the intervention and event onset.
  - c. The event abates when the intervention is discontinued.
  - d. The event reappears upon a re-challenge with the intervention.
2. Not Related (Unlikely, Not Related)
  - a. There is no temporal relationship between the intervention and event onset.
  - b. An alternate etiology has been established.

### 9.3.2 ***Expectedness of AEs***

The Study PI will be responsible for determining whether a SAE is expected or unexpected. An AE will be considered unexpected if the nature, severity, or frequency of the event is not consistent with the risk information previously described for the intervention.

### 9.3.3 ***Severity of Event***

Severity of Event: All reportable AEs will be assessed by a clinician study PI or co-investigator using the following guidelines to quantify intensity:

- 1) Mild: events require minimal or no treatment and do not interfere with the participant's daily activities.
- 2) Moderate: events result in a low level of inconvenience or concern with the therapeutic measures. Moderate events may cause some interference with functioning.
- 3) Severe: events interrupt a participant's usual daily activity and may require systemic drug therapy or other treatment. Severe events are usually incapacitating

## 9.4 **Reporting Procedures**

### 9.4.1 ***Unanticipated Problem (UP) Reporting to IRB and NIDCR***

Incidents or events that meet the OHRP criteria for UPs require the creation and completion of an UP report form. OHRP recommends that PIs include the following information when reporting an AE, or any other incident, experience, or outcome as an UP to the IRB:

- Appropriate identifying information for the research protocol, such as the title, investigator's name, and the IRB project number;
- A detailed description of the AE, incident, experience, or outcome;

- An explanation of the basis for determining that the AE, incident, experience, or outcome represents an UP;
- A description of any changes to the protocol or other corrective actions that have been taken or are proposed in response to the UP.

To satisfy the requirement for prompt reporting, UPs will be reported using the following timeline:

- UPs that are SAEs will be reported to the UCSF IRB (CHR) and to NIDCR within 5 work days of a PI becoming aware of the event.
- Any other UP will be reported to the IRB and to NIDCR within 10 work days of a PI becoming aware of the problem.
- All UPs should be reported to appropriate institutional officials (as required by an institution's written reporting procedures), the supporting agency head (or designee), and OHRP within one (1) month of the IRB's receipt of the report of the problem from a PI.

All UPs will be reported to NIDCR's centralized reporting system via Rho Product Safety:

- Product Safety Fax Line (US): [name]
- Product Safety Fax Line (International): [name]
- Product Safety Email: [rho\\[contact]](mailto:[contact])
- CC Safety Email: [[contact]](mailto:[contact])
- CC Safety Fax Line: [name]

General questions about SAE reporting can be directed to the Rho Product Safety Help Line (available 8:00AM – 5:00PM Eastern Time):

- US: [name]
- International: [name]

#### 9.4.2 ***Serious Adverse Event Reporting to IRB and NIDCR***

In the unlikely event that an AE or SAE incident occurs during this pilot study, any AE meeting the specified SAE criteria will be submitted within 10 work days of a PI's awareness in the UCSF electronic IRB system to the UCSF CHR and on an SAE form to NIDCR's centralized safety system via Rho Product Safety. This report may be sent by fax or email. Once submitted, Rho Product Safety will send a confirmation email to the PIs within one (1) business day. The investigator should contact Rho Product Safety if this confirmation is not received. This process applies to both initial and follow-up SAE reports.

SAE Reporting Contact Information:

- Product Safety Fax Line (US): [name]
- Product Safety Fax Line (International): [contact]
- Product Safety Email: [rho\\[contact]](mailto:[contact])
- CC Safety Email: [[contact]](mailto:[contact])
- CC Safety Fax Line: [name]

General questions about SAE reporting can be directed to the Rho Product Safety Help Line (available 8:00AM – 5:00PM Eastern Time):

- US: [name]
- International: [contact]

The study clinician will complete a SAE form and submit via fax or email within the following timelines:

- All deaths and immediately life-threatening events, whether related or unrelated, will be recorded on the SAE form and submitted to Product Safety within 24 hours of site awareness.
- SAEs other than death and immediately life-threatening events, regardless of relationship, will be reported by fax within 5 work days of site awareness.

All SAEs will be followed until resolution or stabilization.

